### Population

#### Source population

The source population will be selected from the CPRD Aurum. The source population will include all UK National Health Service (NHS) patients (male/female) registered with a participating general practice who are eligible for data linkage. We will not include up-to-standard records because this is not yet available as a measure of data quality in the CPRD Aurum database.

#### Study cohort

We will select a study cohort from the CPRD Aurum to investigate objectives 1–3. We will identify and extract the records in the primary care and HES dataset for all patients with a diagnosis of SMI (hereafter *exposed*) and who are eligible for data linkage. Diagnostic Read codes, which are the standard clinical codes used in UK general practice, will be used to identify an SMI diagnosis. We will also use codes according to the International Classification of Diseases version 10 (ICD-10) from the HES data. The date of the first SMI Read code will be used as the index date, which is the earliest date that an exposed patient may enter the study. From the study cohort, a subcohort of patients will be selected to investigate objective 4. To enter the subcohort, the exposed patient needs a recorded BMI ≥25 kg/m^2^ at any time after the index date. All information will be extracted for the period 01 January 1998 to 31 October 2020—the earliest and latest dates respectively that data are available.

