Examine the association between SMI and weight change.Examine the association between SMI and change in cardio-metabolic risk factors for CVD.Examine the association between SMI and incidence of and mortality from CVD.Compare incidence of advice and offer and actual referral to weight management services in people with both SMIs and BMI ≥25 kg/m^2^ with controls.

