#### Duration of follow-up

Patients will be followed up in the database from their index date until the earliest of the following: date of death; date of outcome of interest; date of leaving the participating practice; date of the latest download of data; or the end of the study follow-up period (ie, up to 22 years).

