#### Comparison group

The unexposed represents the counterfactual and will include patients without an SMI Read code ever (hereafter *unexposed*) drawn from the source population. Up to four unexposed matches will be selected at baseline only if they have a qualifying weight Read code within±one year of the index date to the exposed in which they are matched. The matching variables include: age, sex, practice and calendar time. All weight Read codes will be extracted.

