Health behaviours	Smoking status	Categorical (0=never; 1=ex-smoker; 2=current smoker (light: 1–9 cigarettes/day; moderate: 10–19 cigarettes/day; heavy: 20+ cigarettes/day)). This is coded in GP records. We will use the most recent recorded value of smoking status at the study start date.
	Alcohol use	Continuous (units per week). This is coded in GP records. We will use the most recent recorded value of alcohol use at the study start date.
Demographics	Socioeconomic status (SES)*	Categorical (quintiles)
	Ethnicity†	Categorical (white; Asian or Asian British; black or black British; other ethnic group, mixed)
	Sex†	Binary (0=male; 1=female)
	Age at study entry, in years	Continuous
Physical and/or medical factors	Baseline weight status (body mass index (BMI))	Categorical (normal weight (BMI 18.5–24.9 kg/m^2^); overweight (25.0–29.9); obese (30.0–34.9); severe obesity (35.0–35.9); morbid obesity (40.0–44.9)
	Psychotropic medication	Categorical (antipsychotics (first-generation and second-generation); antidepressants; mood stabilisers)
	Cardio-metabolic medication	Categorical (blood glucose lowering medications; antihypertensive treatments, statins)
We include the following additional variables for objectives 3 and 4 only		
CVD risk factors	Total cholesterol/HDL ratio	Continuous
	Systolic and diastolic blood pressure	Continuous
	Glycaemia	HbA1c/fasting blood glucose (FBG)

*This variable is grouped according to practice level Index of Multiple Deprivation. This is an indicator of material deprivation based on income; employment; health deprivation and disability; education, skills and training; crime; barriers to housing and services; and living environment. It is categorised as quintiles 1–5 with 1 being the most deprived and 5 being the least deprived.

†This variable is grouped according to recommendations by the UK Office for National Statistics.^33 34^

CVD, cardiovascular disease; GP, general practitioner; HbA1c, haemoglobin A1c; HDL, high-density lipoprotein.

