### Statistical analysis

Analyses will be conducted in Stata using an estimation approach. We do not intend to impute missing data. The entry date into the analysis is the index date. The outcome date is the earliest of: (1) the date of death or (2) date of diagnosis of the outcome of interest. For objectives 1 and 2, we will use all repeated measures and run separate models for each analyses. For objective 3, we will use the first recorded diagnosis of the outcome of interest rather than recurrent events. Patients who do not have the outcome of interest will be censored at the earliest of: (1) date of death, (2) date of leaving the practice, (3) date of the latest download of data or (4) the study end date.

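### Objective 4 admits SMI patients on a later BMI record but counts their person-time from the index date, and states no BMI rule for controls

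*Protocol article*

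**What the plan says.** All places are in the protocol article.

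- **Entry, exposed (Study cohort).** The subcohort rule is "To enter the subcohort, the exposed patient needs a recorded BMI ≥25 kg/m^2^ at any time after the index date". It sets no window and does not require the BMI record to precede the outcome.
- **Entry, controls.** The Introduction frames objective 4 as a comparison "in people with both SMIs and BMI ≥25 kg/m^2^ with controls", which attaches the BMI condition to the SMI group. The Comparison group section takes unexposed patients "only if they have a qualifying weight Read code within±one year of the index date" of the exposed patient. It adds "The matching variables include: age, sex, practice and calendar time". BMI is neither a threshold nor a matching variable.
- **Start of person-time.** Study cohort: "The date of the first SMI Read code will be used as the index date". Duration of follow-up: "Patients will be followed up in the database from their index date until the earliest of the following". Statistical analysis: "The entry date into the analysis is the index date". None of these makes an exception for objective 4.
- **Analysis (Primary analyses).** Objective 4 uses a Poisson model on person-time, adjusted for confounders and BMI. Table 2 defines the BMI covariate as baseline weight status in bands, the top two printed as "severe obesity (35.0–35.9); morbid obesity (40.0–44.9".
- **Outcome (Table 1).** The measure is a proportion in each group, with no adjustment stated.

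**The concern.** A rate needs a denominator made up of people who could be counted from the moment counting starts. Here an exposed patient belongs to the denominator because of something recorded later, yet all the time since index is counted. To qualify, the patient must live and remain registered until that record. Because the record need not precede the outcome, a BMI entered at or after a referral can bring a referred patient into the subcohort.

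Controls pass through no such filter. As written, they include people of normal weight, although the Introduction gives a BMI above 25 as the point at which advice or referral is recommended.

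Objective 4 has no other stated comparison, and the Discussion wants it to show whether people with SMI are offered weight support. A rate ratio away from 1 could come from the selection rules rather than from practice.

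**Working it through.** **The plan's own figure.** There is none for objective 4. The only sample size, 3907, is for CVD and does not bear on this point.

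**Inputs for an illustration**

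- r = 20.0 referrals per 1000 person-years (Introduction, general population), taken as the true rate in both groups while BMI is ≥25.
- T = 4.6 years mean follow-up (Sample size calculation). It describes exposed patients with a weight code in the year before index, so it is a proxy.
- s = 0.64, the UK adult share with overweight or obesity (Introduction), as a proxy for the share of control person-time at BMI ≥25.
- w = mean time from index to the qualifying BMI record. The document gives no figure; 0 to 3 years is assumed.
- The referral rate in non-qualifying time is assumed to be zero, then a quarter of r.

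**Formulae (crude, zero rate in non-qualifying time)**

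- Exposed rate = r × (T − w) / T
- Control rate = r × s
- The true rate ratio is 1.

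**Unrestricted controls alone (w = 0).** 20.0 against 20.0 × 0.64 = 12.8, a ratio of 1/0.64 = 1.56.

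**Late qualification, alone and combined with unrestricted controls**

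| w (years) | Exposed rate | Ratio, s = 1 | Ratio, s = 0.64 |
|---|---|---|---|
| 0.5 | 20 × 4.1/4.6 = 17.8 | 0.89 | 1.39 |
| 1 | 20 × 3.6/4.6 = 15.7 | 0.78 | 1.22 |
| 2 | 20 × 2.6/4.6 = 11.3 | 0.57 | 0.88 |
| 3 | 20 × 1.6/4.6 = 7.0 | 0.35 | 0.54 |

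**Non-qualifying time at a quarter of the rate.** The control rate is 20 × (0.64 + 0.25 × 0.36) = 14.6. The exposed rate is 20 × (T − 0.75w)/T, which gives 18.4, 16.7, 13.5 and 10.2. The combined ratios are 1.26, 1.15, 0.92 and 0.70.

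**What BMI adjustment changes.** Three cases need separating.

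1. *A baseline band holding only controls.* Its own category term absorbs it, so it adds nothing to the SMI coefficient. Adjustment removes this part of the dilution.
2. *The normal-weight baseline band.* Exposed patients are in the subcohort only if they later reach a recorded BMI ≥25; controls in that band are unselected. Let q be the share of these controls' person-time at BMI ≥25. Under the zero-rate assumption the within-band ratio is [(T − w)/T] / q, which equals 1 only by coincidence. Baseline BMI cannot correct it, because both groups have the same baseline band.
3. *Bands at or above 25.* The person-time start is still index, and exposed patients must still survive and stay registered until a further record. Adjustment does not touch this.

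The Table 2 bands also leave 36.0–39.9 and ≥45 without a category. Both ranges lie inside the objective 4 population.

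**The case against.** The strongest reply is that BMI is already in the Poisson model, so 1.56 is not the planned estimate. This largely stands for dilution by normal-weight controls. A reader might infer that adjustment must fail because no exposed patient has a BMI below 25. The document does not support that: the covariate is baseline BMI, exposed patients may be below 25 at baseline, and a control-only band would not bias the SMI coefficient. What adjustment leaves untouched is the start of person-time and the selection on later weight gain.

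A reader might also call the wait immortal time. That is too strong. It is immortal for death and for leaving the practice, but a referral can be coded before the first qualifying BMI. A patient already overweight at index may have been eligible for referral throughout. The zero-event assumption is therefore an extreme.

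The numerical inputs are also proxies. Controls are chosen for having a weight code, and the Discussion notes that testing may be more regular in people with overweight, so the share at BMI ≥25 may exceed 64%. At assumed shares of 75% or 85%, the crude inflation is 1/0.75 = 1.33 or 1/0.85 = 1.18.

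Finally, the text leaves some room. The Study cohort section calls the index date the earliest possible entry, and the authors may intend the same BMI rule for controls; a fuller protocol may say so. But the article then fixes entry at index without exception, and a matching BMI rule for controls would still leave the person-time problem.

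**Conclusion.** The point holds as a defect in how the objective 4 groups and their time zero are defined. Followed as written, the plan classifies exposed person-time on a later measurement and compares it with controls selected by a different rule. Adjustment for baseline BMI is a partial remedy. The Table 1 proportions are not stated to be adjusted at all. The Confounding section would judge confounding by comparing estimates with and without adjustment, so part of the selection difference would be read as confounding.

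The size is illustrative only. Crude ratios under a true null run from about 0.5 to 1.6, given the assumed waits of 0 to 3 years, the 4.6-year mean and the 64% proxy. A reader might infer that the SMI rate will be understated, or that the reported ratio will be inflated by 1.56. The document supports neither. Late qualification lowers the exposed rate, unrestricted controls lower the control rate, and qualifying on a BMI recorded after referral raises the exposed rate. The net direction cannot be determined. Objectives 1 to 3 do not use this entry rule.

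**What to change.** - Require a recorded BMI ≥25 kg/m² on or after the index date (matched index date for controls) in both groups.
- Start each person's follow-up at that qualifying record, or treat BMI ≥25 status as time-varying, and count only outcomes from then on. Use the same denominator for the Table 1 proportions.
- Adjust for age, sex, calendar time, practice and the qualifying BMI. Enter BMI as a continuous term, or in bands that close the 36.0–39.9 and ≥45 gaps.

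The cost is protocol wording and a re-derived subcohort. The Comparison group section says all weight codes will be extracted and the Data source section lists height, so no new extraction should be needed. There will be fewer controls and some broken matched sets. These are better handled by adjustment than by re-matching, which may need controls that were never extracted. The result will then apply to people whose BMI is recorded after index, which should be stated.

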**Methods and analysis:**

In this retrospective cohort study, we will link general practice records from the UK Clinical Practice Research Datalink Aurum database. We will establish a cohort of patients diagnosed with SMI between 1998 and 2020 who are matched with up to four controls on age, sex, general practice and calendar year. We will use multivariable mixed-effects linear regression models and Cox proportional hazard models with sequential adjustment for potential confounders identified by separate directed acyclic graphs.

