### Data source

We will use the Clinical Practice Research Datalink (CPRD) Aurum—a governmental, not-for-profit research service holding anonymised primary care records drawn from participating general (primary care) practices dating back to 1987 (http://www.cprd.com). To date, it encompasses routinely collected patient data records of around 16 million patients who are currently registered with some 700 participating general practices. Patient demographic data (ie, year of birth, sex and ethnicity), characteristics (ie, height, weight, smoking status), symptoms, clinical diagnoses, consultations, referrals, prescribed medications and results of investigations are available.

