#### Exclusion criteria

Patients will be excluded from the cohort(s) if they: have less than 1 year of active data in their participating practice before the index date; and/or who have a Read code for coronary heart disease, congestive heart failure or cardiomyopathy, and/or stroke before the index date. A flow diagram will present the selection and exclusion (with reasons where possible) of patients in the study.

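### Limiting all extracted information to 1998 onward conflicts with records said to reach back to 1987, and lets some long-standing SMI enter as newly diagnosed and some earlier CVD escape the exclusion

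*Protocol article*

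**What the plan says.** Under Study cohort the protocol article states: "All information will be extracted for the period 01 January 1998 to 31 October 2020". It explains these dates as "the earliest and latest dates respectively that data are available". Under Data source it describes CPRD Aurum as holding anonymised primary care records "dating back to 1987".

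Three rules look backwards from the index date:

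- **Time zero (Study cohort):** "The date of the first SMI Read code will be used as the index date".
- **Minimum history (Exclusion criteria):** patients are excluded if they "have less than 1 year of active data in their participating practice before the index date".
- **Prior CVD (Exclusion criteria):** patients are also excluded "who have a Read code for coronary heart disease, congestive heart failure or cardiomyopathy, and/or stroke before the index date".

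The abstract describes the exposed cohort as "patients diagnosed with SMI between 1998 and 2020". The Comparison group section requires that the unexposed have never had an SMI Read code. The article states no SMI-free period before index and no rule for patients whose SMI was first coded before 1998.

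**The concern.** A first-ever code can be dated only as far back as the extracted history reaches. If nothing before 1 January 1998 is extracted, someone with SMI coded in 1990 and again in 1999 appears to be a new case in 1999.

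This matters because time since diagnosis is the time axis of the study. Objective 1 concerns the effect of an SMI diagnosis on weight change, estimated from an SMI-by-time interaction. The Introduction notes that trials link psychotropic drugs to rapid weight gain. Long-standing cases may have had that gain before their apparent time zero, and they must have survived and stayed registered to be re-coded. Mixing them with new cases blurs the trajectory after diagnosis. The mixture varies with calendar period, because false first codes arise mainly among early index dates.

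For objective 3, the prior-CVD exclusion is meant to make the outcome incident. A CVD code seen only before 1998 cannot trigger it.

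**Working it through.** **1. The two start dates.** Data source gives 1987; Study cohort gives 1 January 1998 as the earliest available date. The gap is 1998 − 1987 = 11 years. If 1998 reflects the start of a linked dataset, the conflict remains for these rules, because the index date and the CVD exclusion are both defined by Read codes, which come from the primary care record.

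**2. A patient followed through the rules as written.** SMI first coded in 1990, registered throughout, SMI coded again in mid-1999.

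- Earliest SMI code in the extract: 1999, so the index date is 1999.
- At least 1 year of active data before index: yes, from 1998. The rule asks for active data, not for a year without SMI codes.
- Result: enters as diagnosed in 1999, nine years late.

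If the same patient had CVD coded in 1995:

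- CVD coded again between January 1998 and index: excluded, correctly.
- CVD never coded again: kept, but contributes no false event.
- CVD next coded after index: kept, and counted as incident.

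**3. Whether another provision catches this.** The second analysis under Sensitivity and secondary analyses drops patients with the outcome within 2 years of the SMI code. It would remove some CVD re-coded soon after index, but it does not separate long-standing from new SMI. The Discussion's limitations do not mention truncated history.

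**4. How the problem fades.** If the 1-year rule must be met from records starting on 1 January 1998, the earliest index date is about 1 January 1999. From then to 31 October 2020 is 21.83 years. Assuming index dates spread evenly (not stated in the document), the share with less than k years of possible look-back is (k − 1)/21.83:

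| k | Share |
|---|---|
| 2 years | 1/21.83 = 5% |
| 5 years | 4/21.83 = 18% |
| 10 years | 9/21.83 = 41% |

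These are shares with short look-back, not shares misclassified. The latter would need the frequency of pre-1998 codes and of re-coding, which the document does not give.

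**5. Whether a stricter cohort is affordable.** First, the plan's own figure. Inputs from Sample size calculation: risk 0.03 in the unexposed, RR 1.3 (so 0.039 in the exposed), ratio 0.25, power 80%. I used two-sided alpha 0.05.

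- Pooled risk = 0.8 × 0.03 + 0.2 × 0.039 = 0.0318.
- n(unexposed) = [1.960 × √(0.0318 × 0.9682 × 5) + 0.8416 × √(0.03 × 0.97 + 4 × 0.039 × 0.961)]² / 0.009² = (0.7690 + 0.3561)² / 0.000081 ≈ 15 628.
- n(exposed) = 0.25 × 15 628 = 3907.

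The stated 3907 is reproduced exactly, as the number of exposed patients.

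Now suppose only a fraction of the 135 870 SMI patients remains, with four unexposed each. The fractions are assumptions.

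- 10% kept: 13 587 exposed and 54 348 unexposed. The standard error is 0.001683 under no difference and 0.001815 under RR 1.3. Power = Φ[(0.009 − 1.960 × 0.001683)/0.001815] = Φ(3.14) = 99.9%.
- 5% kept: about 6790 exposed. The same formula gives about 95%.

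**The case against.** The strongest reply is that 1998-2020 may be the study period only. The eligibility wording carries no 1998 floor: first SMI code, any CVD code before index, no SMI code ever in the unexposed. The article gives a reason for 1998, and the Data source section describes the database in general, not necessarily the linked patients studied here. It is also a condensed account, and the full approved protocol is not shown. This stands in part: the document does not settle which start date governs, and one should not assume that 1987 is right. But the sentence covers all information, not only index dates and follow-up. Followed as written it produces false first codes, so it needs correcting even if the intention was sound.

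Two stronger readings are tempting. A reader might infer that look-back is zero for 1998 index dates. If only extracted records count, the 1-year rule removes those patients; if earlier records can satisfy the rule, then earlier history is visible after all. Zero look-back follows from neither. A reader might also infer that all missed pre-1998 CVD becomes incident CVD. The cases in the working show that this needs a next CVD code after index, with none between 1998 and index.

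**Conclusion.** The concern holds in a limited form. The two statements about the earliest data conflict. Taken literally, the extraction rule admits some long-standing SMI as newly diagnosed and leaves some prior CVD undetected. Neither the 1-year active-data rule nor the 2-year sensitivity analysis prevents the SMI misdating.

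The effect is confined to patients with relevant codes before 1998 and weakens as index dates move later. It would be too strong to infer that first SMI or freedom from CVD cannot be established for the cohort as a whole. Nor can a percentage attenuation be claimed. If a fraction p of exposed patients had no further early gain, the gain after diagnosis would shrink by p, but the document gives neither p nor grounds for assuming no further gain, so any figure would only restate the assumption. The size is unknown.

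The conclusion rests on the literal reading of the extraction sentence. Should that sentence define only the study period, the remaining task is to say so and to state that earlier codes are used.

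**What to change.** - Reconcile Data source and Study cohort on the earliest date of the primary care records.
- Keep 1 January 1998 to 31 October 2020 as the window for index dates and follow-up only.
- Use all available earlier coded history, in both groups, to date the first SMI code and to apply the prior-CVD exclusion.
- Exclude patients whose first SMI code predates 1998, in line with the cohort described in the abstract.
- If earlier records truly cannot be obtained, require a stated minimum period without an SMI code before index, and add a sensitivity analysis restricted to incident SMI. This fallback reduces the misdating but does not remove it.

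The cost is a change to the extraction specification for the same patients' records, and the loss of some prevalent SMI patients with their matches. On the figures in the working, that loss does not threaten power for RR 1.3. The change is best made before extraction, since history left out of the extract cannot be recovered in analysis.
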